### Risks

Risks of exercise include falls, musculoskeletal injuries, coronary heart disease events (myocardial infarct, acute coronary syndrome), and other side effects that are generally minor. Our previous experience with similar exercise interventions gives our team considerable expertise on the means to mitigate these types of health risks. Maximal cardiopulmonary testing will be conducted by certified exercise physiologists with a physician on-call and present for high-risk participants and appropriate emergency equipment available. A participant may be withdrawn from the study if a research procedure is judged to be potentially harmful or presents an unacceptable risk of injury to the participant. For example, participants could be withdrawn if they develop an abnormality (e.g., abnormal ECG suggesting an unstable cardiac issue, uncontrolled hypertension) that is judged by a physician associated with the study or the participant’s attending physician to pose a risk to the participant if they continue in the study.

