### Randomization

This study will be a prospective open label with blinded evaluation (PROBE) trial and randomize the participants into one of the following four treatment arms:
Aerobic exercise and health behaviour support: Participants will undergo aerobic exercise training for 6 months and will receive 1-year of individually tailored telephone support after the intervention.Aerobic exercise and no health behaviour support: Participants will undergo aerobic exercise training for 6 months and will not receive health behaviour support during the follow-up 1-year follow-up period (at 18 months).Stretching-toning and health behaviour support: Participants will undergo stretching-toning exercise training and will receive 1-year of individually tailored telephone support after the intervention.Stretching-toning and no health behaviour support: Participants will undergo stretching-toning exercise training and will not receive health behaviour support during the follow-up 1-year follow-up period (at 18 months).

Randomization sequence within blocks will be generated by computer using a random number generator. Randomization will be stratified by age (age > 65 vs ≤ 65 years) and sex with blocked, simple randomization into each of 4 strata for each group of participants as they enter the study. Because enrolment occurs in complete groups of participants (rather than sequentially), randomization will be done in complete blocks such that randomness of allocation is completely preserved. Specifically, recruitment for each study site (e.g., University of Calgary, YMCA Calgary) will be done independently. Once the desired number of participants (8–15 participants) are recruited, baseline testing will be conducted. Participants will be then randomized (the random sequence will be generated by computer: REDCap randomization tool) and immediately start the exercise intervention. Randomized allocation will be completely masked to all study personnel, except the database programmer (study coordinator) who will not participate in any participant or protocol-related activities. Participants will receive a “welcome package” containing their allocation group during the baseline testing visits, in advance of the exercise programme starting date.

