**Fig. 1 Fig1:**
[figure not shown]
Overview of study design and participant flow through the trial

After the completion of the screening procedures, the participants will be randomly assigned to one of the four experimental groups. Following randomization, participants will undergo their first set of cerebrovascular/physiological, neuroimaging, sleep, and cognitive factors and will complete several lifestyle and psychological questionnaires (see Table 2). This battery of assessments will be completed again following the 6-month intervention period and after a 1-year follow-up period.

**Table 2 Tab2:** Schedule of physiological, cognitive, psychological, and neuroimaging assessments for the *Brain in Motion II* trial

Assessment measure	Screening assessments	Visit (months)			
		0	3	6	18

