### Statistical analyses

The primary outcome analysis will use mixed-effects regression analysis to assess the effects of exercise on a composite cognitive score where the aerobic exercise intervention group will be compared to the stretching-toning group while adjusting for the participants’ baseline characteristics (age, sex, MoCA score, years of education, and baseline physical fitness level). The adjusted estimates of the mean change in cognitive composite score for each group will be reported along with the corresponding 95% confidence intervals. Statistical significance will be set at *P* < 0.05, and all tests will be two-sided. The assessment of effect modification (heterogeneity of treatment effect) will be performed with the inclusion of multiplicative interaction terms for age, sex, APOE status, CBF, V̇O_2_max, and sleep quality. A final analysis plan, which includes analyses of the secondary outcomes and strategies for handling missing/incomplete data, will be formalized by the investigators prior to breaking the blind. The data analysis will only begin once data collection is complete.

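### The protocol gives two opposite orders for baseline testing and randomization and hands out the allocation during the baseline visits, so effort-dependent baseline measures can be taken in participants who know their arm

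*Protocol article*

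**What the plan says.** Three statements in the protocol article bear on the order of events.

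- **Randomization section, testing first.** "Once the desired number of participants (8–15 participants) are recruited, baseline testing will be conducted". The next sentence continues: "Participants will be then randomized (the random sequence will be generated by computer: REDCap randomization tool) and immediately start the exercise intervention".
- **Study design section, text under Figure 1, randomization first.** Participants are assigned to one of the four groups once screening is complete, and then: "Following randomization, participants will undergo their first set of cerebrovascular/physiological, neuroimaging, sleep, and cognitive factors". The same battery is repeated after the intervention and after follow-up, so this first set is the month-0 baseline of Table 2.
- **Randomization section, disclosure.** "Participants will receive a “welcome package” containing their allocation group during the baseline testing visits, in advance of the exercise programme starting date".

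The Blinding section says participants cannot be blinded and outcome assessors will be. The Primary outcome section places the composite at baseline, 6 and 18 months. The Statistical analyses section states "The adjusted estimates of the mean change in cognitive composite score for each group will be reported" and lists baseline physical fitness level among the adjustment covariates.

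**The concern.** A baseline value is safe to use in a treatment comparison because the assigned arm cannot have affected it. In an open-label trial that holds only if the value is obtained before the participant learns the arm. Here the text allows the opposite.

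The cognitive battery and the maximal treadmill test both depend on how hard the participant tries. Someone who has just learned which class they drew may try more or less hard, and a blinded assessor will record that effort faithfully. A baseline difference created this way enters the mean change in the primary composite, where it cannot be told apart from a treatment effect. The fitness covariate is exposed in the same way, as are the month-0 measures of CBF, V̇O2max and sleep quality if their baseline values are used as the planned effect modifiers.

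Handing out the allocation at a testing visit may also bring that information closer to blinded assessors. The protocol does not say who hands the package over, so this is a possible risk and no more.

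**Working it through.** **Step 1. The text set side by side**

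| Source | Order stated | Can the arm be known at baseline testing? |
|---|---|---|
| Randomization, enrolment sentences | recruit, test, randomize, start exercise | No, if disclosure follows |
| Study design, under Figure 1 | screen, randomize, first battery | Yes, depending on when the arm is told |
| Randomization, package sentence | arm handed out within the baseline visits | Yes, for any test done after the hand-out |

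The first two rows cannot both be true. The third conflicts with the first, because an allocation cannot be handed out during visits that precede randomization. The term welcome package does not settle the timing: the Eligibility criteria section uses it for material with the consent form sent before the first on-site visit.

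**Step 2. Which analysis inputs are exposed**

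- Exposed: the baseline composite (through mean change and the repeated measures) and baseline fitness.
- Not exposed: age, sex and years of education, which knowing the arm cannot alter, and MoCA, which Table 2 lists as a screening assessment.

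**Step 3. The plan's own sample size figure**

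Inputs from the Sample size section: 264 participants, 80% power, 0.4 SD, correlation 0.6, three measurements, 20% attrition. The test is two-sided at 0.05 (Statistical analyses). For a mixed model with compound symmetry, a contrast at the last visit, and retention of 1, 0.80 and 0.64 (20% lost at each follow-up, an assumption), the variance factor is 1.331875:

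n per group = 2 × (1.96 + 0.8416)² / 0.4² × 1.331875 ≈ 131, or 262 in total, close to 264.

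Reading the 20% as total loss gives 226 to 228. The present point does not depend on this.

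**Step 4. Illustration of size**

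This borrows the protocol's sample size, loss and correlation but uses a simpler two-group contrast than the plan's model.

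- n per exercise group = 264 × 0.8 / 2 = 105.6
- SE, change score = √(2 × (1 − 0.6) × 2/105.6) = 0.123
- SE, baseline-adjusted = √((1 − 0.6²) × 2/105.6) = 0.110
- Bias from a baseline shift d with no shift at 6 months: d for change, 0.6d for baseline-adjusted
- Two-sided rejection rate with no true effect = P(Z > 1.96 − b) + P(Z < −1.96 − b), where b = bias/SE

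For d = 0.10: b = 0.10/0.123 = 0.81 for change and 0.06/0.110 = 0.55 for adjusted. The shift d is assumed; the protocol gives no figure.

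| d (SD) | Change: bias | Change: type I error | Adjusted: bias | Adjusted: type I error |
|---|---|---|---|---|
| 0.05 | 0.05 | 6.9% | 0.03 | 5.9% |
| 0.10 | 0.10 | 12.8% | 0.06 | 8.5% |
| 0.20 | 0.20 | 36.9% | 0.12 | 19.3% |

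If aerobic participants score lower at baseline, the bias favours aerobic exercise; if controls do, it works against it. In that second case, with d = 0.10 and a true effect of 0.4 SD, change-score power in this simple calculation falls from 90% to 68%.

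**The case against.** The strongest reply is that the text shows a contradiction and does not show that any baseline was contaminated. Randomization is not disclosure: the Study design section puts randomization before testing but does not say participants are told then. The package sentence also fits a hand-out at the end of the last visit. If every site tested first and disclosed afterwards, only wording needs repair. This stands, and it is why the point says that baselines can be affected.

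The size is also open to challenge. The Discussion cites a survey in which respondents expected similar cognitive results from aerobic and non-aerobic training, and the comparator is an active class on a similar schedule. Participants know their arm at 6 months in any case, so an expectation effect that was constant over time would cancel in the change. Disappointment among controls would bias against aerobic exercise, not for it. All of this stands, so the figures can serve only as illustration. The survey concerns expected cognitive outcomes, however, and does not address effort on a maximal treadmill test.

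Some readers might infer more than the documents support:

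- **That month-0 tests are eligibility gates, so that post-randomization exclusions will follow.** The Clinical Dementia Rating is mentioned under Eligibility criteria as a previous trial's outcome measure, and Table 2 lists it with risk and protective factors, not screening. Dementia is identified by medical history, TICS-M and, in the Table 1 footnote, IADL. For the treadmill test, the Risks section says only that "participants could be withdrawn if they develop an abnormality (e.g., abnormal ECG suggesting an unstable cardiac issue, uncontrolled hypertension" and is judged to pose a risk. That is a discretionary withdrawal rule, while the PAR-Q+ and the request for physician clearance belong to screening.
- **That assessors are unblinded.** The Blinding and Primary outcome sections state that they are blinded, and nothing says that they see the package.

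**Conclusion.** The contradiction is certain on the face of the text, in two forms: testing before against after randomization, and testing before randomization against disclosure during the testing visits. Figure 1 is not visible here, but it could not make both orders true.

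The consequence is conditional. Where disclosure preceded testing, the primary baseline and the fitness covariate are no longer protected by randomization, and assessor blinding does not restore that protection. Where disclosure followed testing, no bias arises from this source. The document does not settle which happened.

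If it did happen, neither size nor direction is known. The 0.10 SD illustration rests on three assumptions: the shift itself, its absence at 6 months, and the simplified contrast. The bias passes in full only to a pure change score; baseline adjustment passes 60% of it at the protocol's correlation. The point merits correction because a baseline taken after disclosure cannot be repaired later, whereas the order can still be fixed for groups not yet enrolled.

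**What to change.** 1. State one order in both the Randomization and Study design sections: consent and screening, all month-0 assessments, randomization of the group, then disclosure of the arm.
2. Replace the wording that places the hand-out within the baseline testing visits. Disclose the arm after the participant's last month-0 assessment, through someone who does no outcome testing.
3. For groups already enrolled, compare each participant's randomization and disclosure dates with the dates of their baseline tests. This shows whether the problem occurred and in how many people.
4. In the final analysis plan, which the Statistical analyses section says will be completed before the blind is broken, add a sensitivity analysis of the primary outcome limited to participants whose baseline battery preceded disclosure.

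The cost is protocol wording, an ethics notification and possibly a short gap between the last baseline test and the first class. No extra visits or participants are needed. The Trial status section reports that new enrolment was on hold at submission, with completion expected in January 2025, so the order could be fixed before recruitment resumes.

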**Screening**					
Telephone Interview for Cognitive Status – Modified (TICS-m)	✓				
Montreal Cognitive Assessment (MoCA)	✓				
Medical history	✓				
Demographics and health history	✓				
Eligibility screening questionnaire	✓				
Physical Activity Readiness Questionnaire (PAR-Q+)	✓				
Brain Injury Screening Questionnaire (BISQ)	✓				
Sociodemographic questionnaire	✓				
Vital signs		✓	✓	✓	✓
**Cognition**					
Neuropsychological test battery		✓		✓	✓
**Cerebral blood flow**					
Transcranial Doppler ultrasound		✓		✓	✓
**Maximal aerobic oxygen uptake**					
Maximal aerobic capacity test		✓		✓	✓
**Blood biomarkers**					
Blood work		✓		✓	✓
**Genetic risk factors**		✓			
**Risk/protective factors**					
Global Physical Activity Questionnaire (GPAQ)		✓		✓	✓
Diet History Questionnaire		✓		✓	✓
Memory Assessment Clinic Questionnaire (MAC-Q)	✓	✓		✓	✓
Multiple Ability Self-Report Questionnaire (MASQ)		✓		✓	✓
Lifetime Cognitive Activities Questionnaire		✓			
Current Cognitive Activities Questionnaire		✓		✓	✓
Clinical Dementia Rating Scale (CDRS)		✓			✓
Lubben Social Network Scale		✓		✓	✓
Family and Friend Support for Exercise		✓		✓	✓
Physical activity-related autonomy support, persuasion, and pressure		✓		✓	✓
Motivation for leisure time physical activity (BREQ-3)		✓		✓	✓
Adult ADHD Self-Report Questionnaire (ASRS)		✓		✓	✓
Hospital Anxiety and Depression Scale (HADS)		✓		✓	✓
Geriatric Depression Scale (GDS)		✓		✓	✓
Centres for Epidemiological Studies Depression Inventory		✓		✓	✓
Beck Anxiety Inventory (BAI)		✓		✓	✓
Perceived Stress Scale Questionnaire (PSS)		✓		✓	✓
Anxiety Sensitivity Index (ASI)		✓		✓	✓
**Sleep quality**					
Polysomnography and actigraphy		✓		✓	✓
Sleep quality/daytime sleepiness/sleep disorders		✓		✓	✓
Pittsburgh Sleep Quality Index (PSQI)		✓		✓	✓
Epworth Sleepiness Scale (ESS)		✓		✓	✓
STOP-Bang		✓		✓	✓
Insomnia Severity Index (ISI)		✓		✓	✓
Restless Legs Questionnaire		✓		✓	✓
**Health behaviour**					
Motivational Readiness Questionnaire		✓		✓	✓
Exercise Benefits/Barriers Scale		✓		✓	✓
EuroQoL Five-Dimension Quality of Life Scale (EQ-5D-5L)		✓		✓	✓
Exercise Self-Efficacy Scale (EXSE)		✓		✓	✓
Adherence Intent and Self-Regulatory Processes Scale		✓		✓	✓

### Exercise interventions

Exercise sessions will be conducted in a small group (8–15 participants) by supervised by qualified trainers in community gyms and recreation centres (e.g., University of Calgary, YMCA Calgary). Costs associated with travelling will not be covered, but parking will be paid for all the exercise sessions. Trainers will have a background in kinesiology and/or certification as a personal trainer and will be trained with suitable emergency equipment and procedures in place. In the event that any of the assessments identify any concerns, the participant’s family physician will be contacted to help in any further follow-up or the appropriate referral. There will be no compensation to those who suffer harm from trial participation. Participation is voluntary, and participants may withdraw at any time and not suffer any disadvantage or reprisal for withdrawing. The researcher may request a participant to withdraw from the study if a research procedure is judged to be potentially harmful to the participant.

Participants will be asked to maintain a minimum of 80% attendance rate at the exercise sessions. Participants who miss a supervised exercise session will be encouraged to complete the session independently and record the unsupervised session in a personal workout logbook (reviewed regularly by trainers). Participants are asked to complete a fourth session each week on their own in addition to the three supervised sessions. Participants can continue with their normal daily activities, such as taking prescribed medications, and activity pattern. This information will be captured in questionnaires (administered at the beginning, during, and completion of the study), logbooks (to record any additional independent unsupervised exercise), and actigraphy (which is used to track physical activity and sleep). At the end of the exercise interventions, no instructions or stipulations will be provided for continuing to exercise, but those in the health behaviour group are provided with telephone support to help them achieve their individual physical activity and exercise goals.

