### Sample size

Preliminary estimates of the effect sizes for improvement in overall cognition (cognitive composite score) with aerobic exercise training are based on the results of a previous study from our group, the Brain in Motion Study [52], that used similar active intervention and outcome. This study will recruit a total of 264 participants. This power calculation, which is based on a sample size calculation formula for a mixed model for repeated measures data with attrition [53], provides 80% power to detect 0.4 standard deviation between-group difference for an average repeated measurement correlation of 0.6 and three repeated measurements, taking 20% attrition into consideration (based on the *Brain in Motion* Study [52];).

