Despite these strengths, this RCT has two main limitations. The nature of the interventions, aerobic exercise and stretching-toning, precludes a double-blind trial design. It is possible that the cognitive outcomes may be, at least partly, influenced by confounding factors, such as socialization offered by the exercise class, participants’ differential expectations for improvement from one type of exercise, and systematic differences in their motivation to improve in fitness. Although these potential confounding variables are difficult to control in a RCT, a previous study showed that participants’ expectations are very unlikely to drive cognitive improvements due to aerobic exercise training [97]. In this study, Stothart et al. (2014) conducted a large survey to examine if people would expect greater improvements in cognitive functioning after aerobic exercise training compared to a control condition (non-aerobic exercise training). Participants who completed the survey expected similar cognitive performance outcomes after aerobic and non-aerobic exercise interventions [97]. It also remains possible that 6 months of aerobic exercise might not be sufficient in length to positively impact cognitive functioning and/or that 1 year of behavioural support is insufficient in length to observe sustained improvements. The results will need to be compared to intermediate findings of those RCTs with longer exercise intervention and/or follow-up periods [35]. Evidence generated by this RCT would be used to inform conversations with primary and community care stakeholders regarding adaptation or incorporation of behavioural support modelled on what we did into the current and future care programmes.

These limitations notwithstanding the Brain in Motion II Study seeks to gain critical insights into the mechanisms by which exercise training improves cognition in older adults at elevated risk of ADRD and stands uniquely situated to do so by examining a large selection of salient physiological and psychological variables. The importance of answers to these questions cannot be overstated given the devastating magnitude of impact that ADRD currently have in the global ageing population.

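### Exercise is delivered in classes nested within exercise arm, but the sample size makes no visible allowance for within-class correlation and the stated primary model names no class effect

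*Protocol article*

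**What the plan says.** **Delivery.** The Exercise interventions section says "Exercise sessions will be conducted in a small group (8–15 participants"), led by trainers at community sites. The two intervention subsections describe three sessions a week of walking or jogging, or a similar schedule of stretching and toning, for 6 months. The content differs, so I read each class as delivering one exercise type.

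**Enrolment.** The Randomization section has each site recruit independently until 8–15 people are available. They are tested at baseline and then randomized together in complete blocks: "Because enrolment occurs in complete groups of participants (rather than sequentially").

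**Sample size.** "This study will recruit a total of 264 participants". The calculation is "based on a sample size calculation formula for a mixed model for repeated measures data with attrition" and "provides 80% power to detect 0.4 standard deviation between-group difference for an average repeated measurement correlation of 0.6 and three repeated measurements". It also allows for a 20% loss of participants. No class size, ICC or design effect is listed.

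**Primary model.** The Statistical analyses section specifies "mixed-effects regression analysis to assess the effects of exercise on a composite cognitive score", adjusted for age, sex, MoCA score, education and baseline fitness. It names no class, trainer, batch or site term and does not list the random effects. It says a final analysis plan will include secondary outcomes and missing data.

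**The concern.** People who train together for 6 months share trainers, companions and session conduct, so their outcomes may be more alike than those of people in different classes. Because a class belongs to one exercise type, this shared component does not cancel in the aerobic versus stretching-toning comparison. It adds to the variance of that comparison.

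A mixed model with participant as the only random unit would not see this component. It would report a standard error that is too small, and so an interval that is too narrow and a P-value that is too small, on the trial's main result. The power statement would be too favourable for the same reason.

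**Working it through.** **Inputs from the article.** N = 264, so 132 per exercise type; difference 0.4 SD; correlation 0.6; three measurements; 80% power; 20% attrition; two-sided 0.05; 8–15 per session.

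**Input assumed.** ICC 0.01 to 0.05. None is given.

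**1. Reproducing 264.** With independent participants, n per group = 2(1.96 + 0.84)² / 0.4² = 98.1, before allowing for repeated measures and attrition. The nearest match I found is a repeated-measures mixed model with compound symmetry, 20% lost in each follow-up interval (retention 1, 0.80, 0.64) and the contrast at the last visit. Its variance factor is 1.332, so 98.1 × 1.332 = 130.7, rounded up to 131 per group, or 262 in total. The attrition pattern and the choice of contrast are my assumptions. The figure is thus reached with independent participants, leaving no visible room for clustering.

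**2. Class size.** If 8–15 is the size of one class, m is 8 to 15. If a recruited batch of 8–15 is split between the two exercise types, m is about 4 to 7.5. The article does not settle this, so I use 4 and 15 as the extremes.

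**3. Effect of ignoring class.**
- Design effect: DE = 1 + (m − 1) × ICC.
- Reported interval width as a fraction of the correct width: 1/√DE.
- True two-sided type I error: 2[1 − Φ(1.96/√DE)].

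**4. Effect on power**, starting from a nominal 80%: Φ(2.80/√DE − 1.96).

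| Class size | ICC | DE | Width fraction | Type I error if ignored | Power |
|---|---|---|---|---|---|
| 4 | 0.01 | 1.03 | 0.98 | 5.4% | 79% |
| 4 | 0.05 | 1.15 | 0.93 | 6.8% | 74% |
| 8 | 0.01 | 1.07 | 0.97 | 5.8% | 77% |
| 8 | 0.05 | 1.35 | 0.86 | 9.2% | 67% |
| 15 | 0.01 | 1.14 | 0.94 | 6.6% | 75% |
| 15 | 0.05 | 1.70 | 0.77 | 13.3% | 58% |

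At ICC = 0 nothing changes.

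**5. Sensitivity to two simplifications.**
- The table uses class size as formed. With 20% lost, a class of 15 contributes 12: at ICC 0.05, DE = 1.55, type I error 11.5% and power 61%.
- The table uses normal critical values. With classes of 15 there are only 132/15 ≈ 9 classes per exercise type. With about 16 degrees of freedom the critical value is 2.12, not 1.96, which works in the other direction.

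**6. Slack at 6 months.** The primary time point is 6 months, where fewer people will have been lost. With 20% lost by then and independent participants, 264 gives about 83% power (complete cases) to 85% (mixed model). That absorbs a DE of about 1.08 to 1.16. For a class of 11.5, the midpoint of 8–15, this corresponds to an ICC of 0.08/10.5 ≈ 0.008 to 0.16/10.5 ≈ 0.015.

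**The case against.** **The random effects are unstated, not excluded.** The covariates listed are baseline characteristics. A class formed after randomization would not belong among them, and a condensed article may leave the random-effect structure to the analysis plan. This stands, and is why the point is that no class effect is named. It does not rescue the sample size: the article itself states the 80% power and its inputs, and none concerns clustering.

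**The size is assumption-driven.** True. With classes of 4 and ICC 0.01 the effect is slight. Individualized intensity, a fourth unsupervised session each week and independent make-up sessions may all weaken dependence within a class. The article also does not say that class membership is fixed or that one trainer leads a class throughout.

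**The 80% may survive.** A reader might infer that clustering makes the stated power plainly wrong. The documents do not support that. A more favourable reading takes 20% loss (105.6 per group) and correlation 0.6, so the standardized difference is 0.4/√0.8 = 0.447 for change from baseline, or 0.4/√0.64 = 0.5 with baseline adjustment. Power is then 90% or 95% before clustering. At ICC 0.05 it becomes 82% or 90% for classes of 6, and 74% or 83% for classes of 12. Three of these four clustered figures stay above 80%. They do not reproduce the protocol's own calculation, but they show that adjustment may offset part of the loss.

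**Batch, site and season.** A reader might also infer that omitting these narrows the interval. It tends to do the opposite. Batches are randomized in complete blocks, so these factors are largely crossed with exercise type, and leaving out a blocking factor tends to make intervals too wide. Only class or trainer correlation within arm narrows them.

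**The Discussion's remark.** The article lists "socialization offered by the exercise class" among possible influences on cognition. It is offered as possible confounding, so it is not evidence of any particular ICC.

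**Conclusion.** The point holds conditionally. Class is nested within the primary contrast, the sample-size inputs carry no visible allowance for it, and the stated model names no class effect. If the within-class ICC is positive and the model is fitted with participant as the only random unit, the interval for the main effect will be too narrow.

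The size runs from slight to material, as tabulated. Which end applies depends on an ICC that the documents do not give and on a class size that they leave open. It does not follow that the trial is underpowered, since covariate adjustment and the 6-month time point may provide some slack. Nor does it follow that the later analysis plan will omit class.

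**What to change.** - Reconcile the Randomization and Exercise interventions sections on whether 8–15 is the recruited batch or the class. The design effect cannot be set until this is clear.
- Record each participant's class, and trainer where it is stable. The article does not say that this is captured.
- Add to the primary model a random intercept for class within exercise arm, with a small-sample degrees-of-freedom correction such as Kenward-Roger or Satterthwaite, because classes per arm may be few.
- Include recruitment batch/site as a blocking factor, since allocation is made within it.
- Restate power at N = 264 for the reconciled class size over a stated ICC range, for example 0.01 to 0.05, naming the time point and the covariate adjustment.

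No extra participants or visits are needed. Analysis is to begin only after data collection is complete, so the change can still be specified in advance. The cost is some added record-keeping, slightly wider intervals and a less favourable stated power.
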